### Interventions

#### Intervention group

All patients randomized to the intervention group received an educational intervention from the NT and PT and were followed by both during the home program.

##### Nurse program

Before discharge from the hospital, all patients were given instruction about their disease condition. The home-based telesurveillance program [16, 17] is designed to provide multidisciplinary care through structured telephone support and telemonitoring. An intensive NT care management program was created, and a NT followed the enrolled patients for 4 months. NTs perform a weekly intervention mainly through structured appointments (from Monday to Friday from 8:30 a.m. to 4:00 p.m.), collecting information about disease status (blood pressure and body weight measurements) and symptoms (general information). Patients were provided with a pulse oximeter (GIMA, Gessate (MI), Italy), and a portable one-lead electrocardiograph (Card Guard 2206; Card Guard Scientific Survival Ltd., Rehovot, Israel) and instructed on how to transmit the electrocardiogram (EKG) trace via a fixed or mobile telephone line to the NT. Participants in the study were also informed that additional telesupport from the NT, aside from the normal weekly NT call, could be accessed by the patients themselves in the case of urgent need or emergency. Unscheduled contacts could be made, 24 h/day 365 days/year, to the NT on duty in case of symptoms manifesting, signs of possible decompensation, or for any doubt about therapy. The EKG was transferred during each call to the telemedicine center, which stored it and sent it to the hospital unit. At the end of each telephone call, the NT could provide support to the patient, offering advice regarding diet, lifestyle, and medications, and suggesting changes in therapy within patient-adapted criteria previously defined with the cardiologist or pulmonologist supervising the program, and could fix an appointment for consultation with the specialist and schedule the next telephone appointment. All conversations were recorded; EKG tracings, the patient’s clinical data and any suggestions made were recorded in a personal health electronic record by the NT. Medical doctors were consulted before referring any patient to the Emergency Department.

##### Physiotherapist program

Patients were assessed by the PT who designed a personalized rehabilitation program to meet each patient’s particular needs. The level and intensity of physical activity were calculated in a rehabilitation triage schedule (Table 5) adding together dyspnea, meters walked (6MWT), and ADL scores. Based on this score, patients with a score from 0 to 6 were prescribed hard training, while patients with a score from 7 to 12 were prescribed light training. An educational session was held where the PT instructed the patients and their caregivers on how to perform the exercises correctly and described the rehabilitation goals within the training period. Patients were provided with the required instruments (weights, mini-ergometer or cycle-ergometer, pedometer, and physical activity diary) and were instructed in how to utilize them.

**Table 5 Tab5:** Rehabilitation triage schedule

Scores	Dyspnea	6MWT	ADL
0	No dyspnea at usual activity, performed at normal speed, or dyspnea only at extraordinary activity		
1x	Dyspnea at harder activity without pauses (climbing > 3 flights of stairs)	>350 m	Independent
2x	Dyspnea at moderate activity with occasional pauses (walking slightly uphill and climbing <3 flights of stairs	350–300 m	Minimal assistance needed
3x	Dyspnea at mild activity and light exercise with many pauses (walking, washing, standing up)	300–250 m	Moderate assistance needed
4x	Dyspnea at rest, sitting, or lying down	<250 m	Totally dependent

6MWT 6-min Walk Test, ADL activity of daily living

In addition, patients were provided with a pamphlet in which their personalized rehabilitation program was recorded, and a DVD, recorded at our institute, which presented a simulation by the PT of all the exercises prescribed. Recorded on the DVD, each patient could find the training path that they followed during their stay in hospital: callisthenic exercises for different body regions (neck, upper and lower limbs, shoulders, torso), exercises for strengthening of the limbs, gluteal and abdominal muscles, stretching and running-on-the-spot exercises and arm-crank exercises for the upper limbs.

##### Rehabilitation program

The rehabilitation program started after in-hospital rehabilitation discharge; in general, this was 7 days after the patient’s enrollment. The number and intensity of training sessions were adapted during the period of the study, or in the case of problems reported by patients, during telephone contacts.

The “light training” rehabilitation program consisted of:15–25 min of exercise with a mini-ergometer without load three times/week30 min of callisthenic exercises three times/weekFree walking twice a week

The “hard training” rehabilitation program consisted of:30–45 min of mini-ergometer with incremental load (from 0 to 60 watts max), from 3 to 7 days per week30–40 min of muscle reinforcement exercises using 0.5-kg weights, 3 to 7 days per weekPedometer-based walking, from 2 to 7 days per week. The pedometer provided numerical feedback so that the number of steps could be increased week by week (increase predicted: 10 % per week)

During the 4 months of training, the program at home was targeted to reach a moderate or high level of dyspnea and/or muscle fatigue according to the Borg scale at the end of any training session. Based on this assessment, the PT could decide to increase or maintain the workload. Patients were asked to write down the physical activity performed daily in a diary and to report it during the next telephone appointment.

The PT contacted the patient by telephone once a week. During each scheduled telephone contact, the PT gathered information about the patient’s general clinical condition (e.g., asthenia, muscle, and joint pain), physical activity performed during the week (duration of exercises and number of steps walked), and clinical parameters before and after training (blood pressure, heart rate, oxygen saturation, and Borg scale score). The PT verified the training level of physical activity performed and planned the rehabilitation targets for the following week (weight use, increase in number of steps, and duration of exercise). During the telephone call, the PT also gave extra reinforcement on the value of lifestyle changes and the importance of exercise. At the end of each call, the PT entered the data into a personal health electronic record.

#### Control group

On discharge from in-hospital rehabilitation, patients in the control group received the standard care program including medications and oxygen prescription, visits from the general practitioner, and in-hospital check-ups on demand. Patients were free to conduct physical activity without any monitoring or reinforcement provided by the hospital. At study enrollment, patients were instructed in an educational session about the desirability of maintaining a healthy lifestyle and were invited to practice daily physical activity as preferred.

### Telemedicine Service Center

A Telemedicine Service Center (HTN, Brescia, Italy) provided technological support, biomedical devices, and a call center to provide telemonitoring activities, a database for the data collected (TelMed platform), and clinical and nursing support during the night and at weekends through its health personnel, thus guaranteeing the 24 h/day service.

### Outcome assessments

The primary outcome was exercise tolerance improvement measured by difference in the meters walked in the 6MWT. The secondary outcomes were: (1) reduction of hospitalizations for cardiovascular and/or respiratory diseases, (2) reduction of hospitalizations for all causes, (3) improvement of QoL in the MLHFQ and the CAT, (4) reduction in impairment/disability evaluated by the Barthel Index, (5) reduction in dyspnea evaluated by the MRC scale, (6) reduction in dyspnea and fatigue at rest evaluated by the Borg scale, (7) improvement of physical activity profile evaluated by the PASE questionnaire and daily steps reported by patients, and (8) improvement of oxygenation (PaO_2_/FiO_2_).

In the intervention group only, we also evaluated: (1) adherence to at least 70 % of the prescribed rehabilitation sessions, (2) qualitative evaluation of patients’ compliance to the rehabilitation program, (3) use of health services, calculated as total and per-person number of PT and NT scheduled and unscheduled calls, total and per-person number of PT home visits, total and per-person number of educational sessions, and total and per-person time spent by the PT and NT in the study.

### Withdrawal

According to Italian research ethics legislation, we informed the patients about their rights as subjects in a scientific trial and about their discontinuation rights. We do this to make patients consider participation thoroughly to diminish the likelihood of their dropping out. Patients can withdraw from the trial at their own request or at the request of their legal representative at any time. Every withdrawal was recorded in the patient’s “personal health record” (TelMed).

### Data collection, management, and analysis

We collected and managed study data using a shared web platform (TelMed) made available by the Telemedicine Service Center. Only relevant staff have logged access to the key file.

The principal investigators from each scientific discipline have a shared responsibility to secure and monitor data collection and interpretation, and thus they are all involved in project management, analysis of samples, data collection, and observations and will all have access to the final dataset and be jointly involved in the interpretation of results.

### Adverse events monitoring

All adverse events that occurred during the 6-month study observation period will be reported in the final paper. A serious adverse event is defined as any untoward medical occurrence resulting in hospitalization or prolongation of hospitalization, or which results in a life-threatening problem, death, or disability. Adverse events will be defined as any untoward occurrences in study participants, potentially related to implementation of the study protocol. All serious and unexpected adverse events will be reported to the Ethics Committee as required.

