**Methods/designs:**

Patients, after inpatient rehabilitation, were randomly assigned to the intervention or control group, followed for 4 months at home, then assessed at 4 and 6 months. The intervention group followed a telesurveillance (telephone contacts by nurse and remote monitoring of cardiorespiratory parameters) and home-based rehabilitation program (at least three sessions/week of mini-ergometer exercises, callisthenic exercises and twice weekly pedometer-driven walking, plus telephone contacts by a physiotherapist). Telephone follow-up served to verify compliance to therapy, maintain exercise motivation, educate for early recognition of signs/symptoms, and verify the skills acquired. At baseline and 4 and 6 months, the 6-min Walk Test, dyspnea and fatigue at rest, oxygenation (PaO_2_/FiO_2_), physical activity profile (PASE questionnaire), and QoL (Minnesota and CAT questionnaires) were assessed. During the study, serious clinical events (hospitalizations or deaths) were recorded.

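### The adverse-event definition requires relatedness to the protocol but the serious-event definition does not, so the two do not nest and non-serious counts tilt toward the intervention arm

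*Protocol article*

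**What the plan says.** Under Adverse events monitoring, the protocol article gives two definitions that do not match. For adverse events: "Adverse events will be defined as any untoward occurrences in study participants, potentially related to implementation of the study protocol". For serious adverse events: "A serious adverse event is defined as any untoward medical occurrence resulting in hospitalization or prolongation of hospitalization", or an event that is life-threatening, disabling or fatal, with no mention of cause. The same section commits to publication: "All adverse events that occurred during the 6-month study observation period will be reported in the final paper".

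The arms differ in how much protocol activity they receive after discharge. Intervention patients have home training, a pulse oximeter and a portable electrocardiograph, a weekly nurse contact and unscheduled access at any hour (Nurse program, Rehabilitation program). The article also says: "The PT contacted the patient by telephone once a week". Of controls it says: "Patients were free to conduct physical activity without any monitoring or reinforcement provided by the hospital". At enrollment controls had an education session and were "invited to practice daily physical activity as preferred". They also undergo the study assessments shown in Table 2.

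Serious outcomes are collected separately and without a causal condition. The Abstract states: "During the study, serious clinical events (hospitalizations or deaths) were recorded". Outcome assessments lists cardiorespiratory hospitalizations, and also "2) reduction of hospitalizations for all causes", as secondary outcomes.

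**The concern.** Causality is normally an attribute recorded about an event after it has been captured. Here it is an entry condition. In an open trial where one arm receives nearly all the post-discharge protocol activity, that condition does not act equally on the two arms. Joint pain at home can readily be linked to prescribed training in an intervention patient. The same pain at home in a control patient has little protocol activity to be linked to, so it would often not count.

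What is at stake is the reading of non-serious harms. A reader of a randomized trial will compare the reported counts by arm whether or not a test is planned, and part of any difference would come from the definition. The rule is stated outright, so this is not a detail left to a fuller document. A later analysis plan cannot restore events that the definition kept from being recorded.

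**Working it through.** No figure in the article describes adverse-event frequency, so there is no stated figure to reproduce. The check is a comparison of the two definitions, followed by an illustration on assumed inputs.

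**Step 1: do the definitions nest?**

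| Event | Meets serious definition | Meets adverse-event definition |
|---|---|---|
| Serious, potentially protocol-related | yes | yes |
| Serious, unrelated | yes | no |
| Non-serious, potentially protocol-related | no | yes |
| Non-serious, unrelated | no | no |

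The second row is the inconsistency: a serious adverse event that is not an adverse event. Read literally, the promise to report all adverse events does not cover it. It is also unclear whether the duty to report serious and unexpected adverse events to the Ethics Committee does. The fourth row is where non-serious events are lost, and controls will tend to have more of their events there.

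**Step 2: what protocol exposure does each arm have?**

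- Intervention: four months of home training, devices, nurse advice and physiotherapist guidance, plus the study assessments.
- Control: the 6-min Walk Test at T0, T1 and T2, arterial blood gases at T0 and T1 (Table 2), and the education session with its invitation to be active.

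The control column is not empty, but it consists of isolated occasions against four months of continuous activity.

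**Step 3: opportunity to learn of events.** This is a separate mechanism that acts in the same direction. Four months is 4 × 52.2 / 12 = 17.4 weeks. One nurse contact and one physiotherapist call a week give about 17 + 17 = 34 scheduled contacts per intervention patient. The article describes no scheduled study calls for controls between visits. This imbalance would remain if the definition were corrected, so it does not measure the effect of the definition. It does limit which events can be compared afterwards.

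**Step 4: illustration of the definition's effect.** Let n be patients per arm, r the true risk of a non-serious event (equal in both arms), and f the fraction of events judged potentially related. Expected counted events are n × r × f, and the apparent ratio is f(intervention) / f(control), whatever n and r are. Take n = 55 (the lower planned enrollment per group, from Sample size) and assume r = 0.20 and f(intervention) = 0.50. The values of r and f are assumptions.

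| f(control) | Intervention count | Control count | Apparent ratio |
|---|---|---|---|
| 0.05 | 55 × 0.20 × 0.50 = 5.5 | 55 × 0.20 × 0.05 = 0.55 | 10 |
| 0.10 | 5.5 | 1.1 | 5 |
| 0.25 | 5.5 | 2.75 | 2 |
| 0.50 | 5.5 | 5.5 | 1 |
| No relatedness condition | 55 × 0.20 = 11 | 11 | 1 |

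With r = 0.40 the counts double and the ratios are unchanged. Serious events do not enter this calculation, because their definition has no such condition.

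**The case against.** The strongest reply is that the main safety information is untouched. Serious events, deaths and hospitalizations are captured in both arms regardless of cause. A reader might infer that safety cannot be compared between arms at all, or that the control count will be near zero whatever happens. The documents do not support either inference. The effect is confined to non-serious events. Controls also have protocol procedures to which an event could be attributed, and being potentially related is a low threshold.

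Second, a reader might infer that a biased between-arm adverse-event analysis is planned. None is stated: adverse events are not among the listed outcomes, and Statistical analysis names no contrast for them. The article promises only to report them.

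Third, a reader might infer that unblinded staff decide relatedness. The article names no assessor. Under Randomization it says patients and physicians were not blinded but outcome assessors and data analysts will be.

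Fourth, the contact imbalance is inherent in comparing telesurveillance with usual care, and the illustration in the working includes the case of no distortion.

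All four limits are accepted. Two things remain. The definitions conflict as written, and the relatedness condition is easier to meet in the arm that carries most of the protocol activity.

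**Conclusion.** The point holds for non-serious events and for the consistency of the two definitions. A serious event unrelated to the protocol falls outside the adverse-event definition, and following the rule tilts non-serious counts toward the intervention arm.

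The direction rests on one assumption: an event at home is more readily judged potentially related when the patient is on the home program than when not. The size is unknown. The illustrated range, a ratio of 10 down to 1, depends entirely on assumed fractions and is not an estimate for this trial. The primary outcome, the sample size and the stated analyses are unaffected. It is worth correcting because the resulting counts are to be published and the change is small.

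**What to change.** Define an adverse event as any untoward medical occurrence in a participant in either arm, whatever its relation to the protocol. Make serious adverse events an explicit subset, and record relatedness as a separate attribute of each event.

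Base any between-arm safety statement on serious events. Add non-serious events only if they were elicited in the same way in both arms at T1 and T2. Report events learned through the intervention calls as descriptive data for that arm, labelled as such. If non-serious events in controls were not collected, say so in the paper.

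The cost is rewording one definition and rearranging the safety reporting. The drawback is timing: Trial status says follow-up ended in April 2015, so identical questioning can no longer be introduced and the between-arm comparison may be limited to serious events. Any non-serious control events obtained at T1 and T2 would also rest on patients' recall.

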### Sample size

A priori sample size was calculated based on previously published randomized controlled trial (RCT) data on COPD and CHF rehabilitation [29, 30] using primary outcome. With an estimated improvement at T1 with respect to T0 in the treatment group of 30 ± 50 m (mean ± standard deviation (SD)) on the 6MWT and no change expected in the control group (0 ± 50 m), at 80 % of power and a significance level of *p* < 0.05, our RCT would need a sample size consisting of at least 44 participants in each group. By taking the probability of dropouts into account (20–25 % of enrolled patients), we decided to include at least 55–60 patients in each group.

### Statistical analysis

Statistical analysis will be carried out by a certified health professional using STATA 13.0 software (College Station, TX, USA). Data will be descriptively analyzed and presented as percentage or mean ± standard deviation for all clinical variables, median ± interquartile (IQ) range for variables without a normal distribution, and percentage for categorical and binary variables. Distribution and normality of variables will be tested by the Kolmogorov-Smirnov test. To compare groups at T0, Student’s *t* test or the Mann-Whitney-Wilcoxon test for continuous variables, and the chi-squared test for categorical variables, will be used.

The effects of training will be analyzed by two-way analysis of variance (ANOVA) for repeated measures (time and group). A post hoc analysis will be conducted when the ANOVA F ratio is significant for Student’s *t* test among times and groups, and Bonferroni’s correction will be applied.

Also, predictive analysis will be performed to detect the characteristics of improvers and nonimprovers using multivariate logistic regression.

The level of significance will be set at *p* < 0.05.

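### The only stated effect analysis, a time-by-group ANOVA with t tests, uses the T0 value inefficiently for the Barthel, MRC and Borg outcomes and gives no fallback if scores are strongly skewed

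*Protocol article*

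**What the plan says.** The Statistical analysis section gives one method for the treatment comparison: "The effects of training will be analyzed by two-way analysis of variance (ANOVA) for repeated measures (time and group"). If F is significant, Student's t tests among times and groups follow, with Bonferroni correction.

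The same section plans Kolmogorov-Smirnov tests of normality and reports the median and interquartile range for non-normal variables. A choice of test by distribution appears only for T0, where Student's t test "or the Mann-Whitney-Wilcoxon test for continuous variables, and the chi-squared test for categorical variables, will be used". The logistic regression looks for predictors of improvement and does not compare the arms.

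The secondary outcomes include "4) reduction in impairment/disability evaluated by the Barthel Index, (5) reduction in dyspnea evaluated by the MRC scale", and then dyspnea and fatigue on the Borg scale. Table 2 schedules all three scales at T0, T1 and T2, and the Trial structure section places randomization after the T0 assessments. The first two secondary outcomes are "1) reduction of hospitalizations for cardiovascular and/or respiratory diseases, (2) reduction of hospitalizations for all causes". These are events recorded during the study, and Table 2 does not list them as a visit measurement.

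**The concern.** There are two gaps for the Barthel, MRC and Borg outcomes.

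- **Use of T0.** With arms formed by randomization, the time-by-group contrast between T0 and T1 equals a two-sample comparison of change scores. That fixes the weight on the T0 value at one. A model with T0 as covariate estimates the weight, and it is more precise whenever the correlation between visits is below one. T0 is measured before randomization, so it is a legitimate covariate.
- **No fallback after T0.** The normality check can alter the test used for the baseline table but not the test used for the effect, which is where it would matter more.

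At stake is power for secondary outcomes 4 to 6, in a trial sized for the 6MWT alone.

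**Working it through.** **1. The plan's own figure.** Inputs from the Sample size section: "improvement at T1 with respect to T0 in the treatment group of 30 ± 50 m", "no change expected in the control group (0 ± 50 m"), and "at 80 % of power and a significance level of" p < 0.05. The section does not state whether the test is one- or two-sided.

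- Two-sided: n = 2 × (1.96 + 0.8416)² × (50/30)² = 43.6, so 44 per arm. One-sided gives 35, so two-sided is meant.
- Exact t power at 44 is 79.5%, and at 45 it is 80.4%.
- Dropout: 44/0.80 = 55 and 44/0.75 = 58.7, so 59.

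The planned size reproduces, and nothing below changes it.

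**2. Why T0 adjustment helps.** Take equal SD σ at both visits and correlation ρ.

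- Variance of the arm difference in change: (2/n) × 2σ²(1 − ρ).
- Variance with T0 as covariate: (2/n) × σ²(1 − ρ²).
- Ratio of the second to the first: (1 + ρ)/2.

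Normal-approximation power with n = 44 and an assumed shift of 0.5 SD is Φ(0.5/SE − 1.96):

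| Assumed ρ | Ratio | Change score | T0 as covariate |
|---|---|---|---|
| 0.5 | 0.75 | Φ(0.385) = 65% | Φ(0.748) = 77% |
| 0.6 | 0.80 | Φ(0.662) = 75% | Φ(0.971) = 83% |
| 0.7 | 0.85 | Φ(1.068) = 86% | Φ(1.324) = 91% |

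The gain is about 5 to 12 points on a continuous score. Cutting a score into categories or capping it lowers the observed correlation, so the gain on such scales tends to be larger.

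**3. Simulation on ordinal and bounded scores.** There were 44 per arm, latent shift 0.5 SD, latent correlation 0.6 and 1,000 runs per cell (Monte Carlo standard error about 1.6 points). The documents give no score distributions, so every shape is an assumption.

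| Assumed shape | t on change | Mann-Whitney on change | Linear, T0-adjusted | Rank, T0-adjusted |
|---|---|---|---|---|
| Symmetric, five levels | 63% | 61% | 76% | 74% |
| About 50% at ceiling | 41% | 39% | 56% | 56% |
| About 70% at ceiling | 27% | 25% | 36% | 40% |
| Skewed with ceiling | 29% | 35% | 45% | 57% |

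- From t on change to the linear T0-adjusted model, the gain is about 10 to 17 points (smallest with about 70% at ceiling, largest with the skewed ceiling: 28.9% to 45.4%).
- From linear to rank, both adjusted, it is −2, 0, +4 and +11 points (45.4% to 56.5% in the last row). Ranks clearly matter only under strong skew at a bound.
- With no effect, the t test on change rejected in 4.4% to 4.8% of runs on these shapes.

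**4. Three visits.** A separate simulation at 44 per arm, also with assumed distributions, included the planned time-by-group F test. Across its scenarios power was 33–78% for F, 32–74% for t on change and 48–82% with T0 adjustment, with type I error about 5%. The F test over three visits therefore does not recover the loss.

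**The case against.** The strongest defence is that the stated method is valid: it holds its type I error, and t tests on change did as well as rank tests on change unless the skew was strong. This stands. A reader might infer that ANOVA is wrong for any ordinal scale. The figures do not support that: on the symmetric five-level scale the linear T0-adjusted model was as good as the rank one. Most of the gain comes from T0, not from changing the type of model.

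Second, the shapes are assumed. This also stands. The article gives no score range or expected distribution for these scales. It describes the patients as frail and disabled, which sits uneasily with many at full Barthel independence. It refers to Borg at rest under Outcome assessments but in daily activities under Trial structure, so a pile-up at zero cannot be predicted. Proportional odds was not simulated; the rank model stands in for it.

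Third, a reader might infer that skewed scales will be described only by means. The plan provides the median and interquartile range, so that reading fails.

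Fourth, a reader might infer that the hospitalization results cannot be produced, or that they will be biased by unequal follow-up. Neither follows. The events are recorded and can be compared by ordinary methods. The ANOVA sentence concerns the effects of training and does not claim hospitalizations. No comparison of raw counts is planned, and no difference in loss between arms is stated. An article may leave this method to a fuller document.

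**Conclusion.** The point holds as a matter of efficiency and of a missing fallback, limited to the Barthel, MRC and Borg outcomes. The one stated effect analysis gives up about 10 to 17 points of power against a linear T0-adjusted model at 44 per arm, under an assumed latent shift of 0.5 SD, latent correlation of 0.6 and the four assumed shapes. A further 11 points or so is available from a rank form only if scores are strongly skewed against a bound. A smaller shift or a higher correlation between visits would change these figures; the direction comes from the variance ratio (1 + ρ)/2, which is below one for any ρ < 1.

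Type I error, the primary outcome and its sample size are not affected. On hospitalizations there is only a minor note: events do not fit a time-by-group ANOVA, and the article is silent on what will be used.

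**What to change.** In the Statistical analysis section, state that Barthel, MRC and Borg are compared between arms at T1 (and at T2) by a model with the T0 value as covariate. State that where scores are heavily skewed or bounded, a rank-based or ordinal version, also adjusted for T0, is used, and set the criterion for that choice in advance without reference to arm. Report each effect with a 95% CI.

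As an optional addition, name a rate model with time at risk as offset for hospitalizations, if a fuller document does not already do so.

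The cost is analysis wording only: no new data, patients or visits. An ordinal effect measure is less familiar to clinicians than a mean difference. Trial status says follow-up has ended and data are being processed, so the change should be dated and made while the analysts are still blinded; if made later, it should be reported as a post hoc choice beside the planned ANOVA.
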